### Site selection and sample size rationale

We will purposely select six National Health Service (NHS) hospitals across England to participate in the study. All centres who have been using the DEKODE platform for at least twelve months will be invited to participate in this research. From this, three centres who are interested to participate in the study following informed consent will be included on a first come basis. Similar, all new interested in joining the DEKODE surveillance system will be invited to participate in the study as well. The three centres interested to participate after informed consent will be included in the study on a first come basis as well. This sampling strategy is designed to capture implementation processes across sites with varying levels of experience, organisational structures, resources, and clinical workflows. This approach balances practical feasibility of delivering the evaluation with the need to explore variability, enhancing the transferability of findings to broader NHS settings.

The number of participating centres was selected pragmatically to balance feasibility with the need to capture variation in organisational context, clinical workflow, and implementation maturity. The inclusion of three early adopter sites is informed by previous DEKODE work, in which data from 177 DKA episodes across three hospitals were used to evaluate variation in DKA care processes, examine factors influencing length of stay and test quality improvement interventions. Although that study did not demonstrate a significant reduction in. DKA duration or length of stay, it demonstrated the feasibility of using a three-hospital DEKODE dataset to support multi-side audit, benchmarking, and quality improvement. The present study expands this approach by including three early adopter sites and three new implementer sites, enabling comparison across different levels of implementation maturity and hospital context. For the quantitative component, all eligible adult DKA episodes identified during the baseline, implementation, and follow-up periods will be included, with the final number determined by site-level DKA admission volumes.

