### Quantitative data collection and outcomes

The study will include a six-month baseline period prior to DEKODE implementation or evaluation (January to June 2026), a six-month active implementation phase (July to December 2026), and a twelve-month follow-up period (January to December 2027). This proposed timeline is informed by previous DEKODE evaluations, in which improvements in DKA care episode duration were detectable within a comparable follow-up period after implementation (11). An interrupted time series (ITS) design will be applied to assess changes in outcomes attributable to DEKODE implementation.

The primary quantitative outcomes include the DKA episode duration, defined as the time from diagnosis to biochemical resolution; adherence to the Joint British Diabetes Societies (JDBS) guidelines for DKA between 80% and 120% of the recommendations, such as timely initiation of insulin treatment, adequate fluid resuscitation, and appropriate biochemical monitoring; and the occurrence of iatrogenic complications, including hypokalaemia and hypoglycaemia. In addition, we will assess key clinical outcomes, namely in-hospital mortality, 30-day readmission rates for DKA, and overall length of hospital stay. Secondary outcomes will focus on comparative performance between early adopter and new implementer sites, as well as site-level variation relative to the collective dataset, enabling benchmarking across participating hospitals.

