### Quality improvement and implementation measures

The practical improvement component of DEKODE will be informed by concepts from the Model of Improvement (31). The specific aims are to reduce unwarranted variation in DKA care across participating centres and to understand how DEKODE is implemented, adapted, and sustained in different hospital contexts.

These aims will be addressed through mixed-methods approach. Quantitative audit data will be used to examine DKA process and clinical outcomes. Process measures will include adherence to key components of DKA management, including timely initiation of insulin, appropriate fluid replacement, ketone monitoring, glucose monitoring, and potassium monitoring. Clinical outcome measures will include time to DKA resolution, length of hospital stay, hypoglycaemia, hypokalaemia, intensive care admission, 30-day readmission, and mortality.

Qualitative data from healthcare professionals involved in DKA care, patients recently hospitalised with DKA and carers or family members where appropriate will be used to explore perspectives on DKA management and implementation experiences. This will include perceived adoption, fidelity, feasibility, acceptability, local adaptations, barriers, and facilitators to DEKODE implementation and sustained use.

Balancing indicators will include unintended consequences of implementation, such as additional data collection burden, variable clinician engagement with feedback and potential impact on local workload. Implemented changes will be monitored through quarterly feedback reports, monthly cross-site meetings, and real-time communication between participating centres and the central DEKDOE team. These mechanisms will allow local teams to review progress, identify barriers, refine improvement actions, and adapt implementation strategies according to local context.

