## Discussion

This study contributes to implementation science by offering a detailed, theory-informed method for embedding a scalable digital audit and feedback system within routine acute care pathways. By explicitly integrating established frameworks such as IRLM, the method provides a structured approach to identify the contextual barriers and facilitators that influence DKA care, systematically link these facilitators and barriers to targeted implementation strategies, and map the mechanisms through which these strategies improve both process and clinical outcomes. Our approach ensures that DEKODE is not applied in isolation but is tailored to local workflows, resource availability, and organisational culture. Unlike approaches that focus solely on clinical effectiveness or isolated quality improvement projects (37, 38), this framework-driven design allows DEKODE to address the root causes of variability in DKA care, enabling consistent, scalable improvements across diverse hospital settings. Applied to DKA care, DEKODE is expected to reduce variation in practice, enhance protocol adherence, and thereby indirectly improve patient outcomes across diverse hospital settings.

For researchers, our study provides a replicable model to evaluate digital interventions in healthcare, emphasising mixed methods approaches and rigorous framework application. Practitioners may benefit from actionable insights into how data-driven feedback can be integrated to enhance clinical workflows and patient outcomes (14, 18).

A key implementation challenge will be translating the DEKODE model from a theory-informed digital audit-and-feedback intervention into routine clinical practice across hospitals with different levels of organisational maturity, staffing capacity, digital infrastructure, and safety culture. Although standardised data collection and feedback reports provide a common structure, sustained improvement is likely to depend on local ownership, multidisciplinary engagement, and the ability of teams to act on feedback within existing governance and quality improvement structures. Sites may vary in their readiness to engage with performance feedback, their capacity to complete data collection, and their ability to implement improvement actions in response to identified care gaps. These factors may influence both the fidelity and sustainability of DEKODE implementation.

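### One two-sided 80–120% band scores a timing, an amount and a frequency item alike, so the adherence outcome can understate an improvement, or show it as a decline where baseline care is near target

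*Protocol article*

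**What the plan says.** The Protocol article, Methods, Quantitative data collection and outcomes, lists the primary quantitative outcomes. The list opens with episode duration: "The primary quantitative outcomes include the DKA episode duration, defined as the time from diagnosis to biochemical resolution". The second is adherence to the JBDS "guidelines for DKA between 80% and 120% of the recommendations, such as timely initiation of insulin treatment, adequate fluid resuscitation", and the sentence continues "and appropriate biochemical monitoring; and the occurrence of iatrogenic complications, including hypokalaemia and hypoglycaemia". The band and the three example items (insulin timing, fluid, monitoring) therefore stand in one clause.

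The same section says how the outcomes are analysed: "An interrupted time series (ITS) design will be applied to assess changes in outcomes attributable to DEKODE implementation". The Discussion gives the expected direction: "DEKODE is expected to reduce variation in practice, enhance protocol adherence, and thereby indirectly improve patient outcomes across diverse hospital settings".

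The section Quality improvement and implementation measures lists the process measures again, as "adherence to key components of DKA management, including timely initiation of insulin, appropriate fluid replacement, ketone monitoring, glucose monitoring, and potassium monitoring". It gives no band, no direction and no rule for any single item. Nothing elsewhere in the article exempts an item from the band or says how the percentage is formed.

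**The concern.** The three items differ in kind. A fluid volume may be a target amount, where too much and too little are both departures. Timely insulin reads naturally as an upper limit on a time. A monitoring frequency may be a minimum number of checks. A two-sided band suits the first kind. For the other two it places a large departure in the favourable direction in the same failing category as a departure in the unfavourable one.

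This affects a primary outcome whose change over time is to be attributed to the intervention and is expected to be a rise. If hospitals become faster or monitor more closely, the score can rise by less than it should, stay flat or fall.

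**Working it through.** **What the percentage can mean.** A share of recommendations met cannot exceed 100%, so an upper bound of 120% would be empty under that reading. The coherent reading is the ratio r = delivered ÷ recommended, with an item adherent when 0.8 ≤ r ≤ 1.2. The article does not spell out r for a timing item. I take it as actual time ÷ recommended time T.

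**Inputs.** From the article: the 80% and 120% limits and the three items. It gives no recommended times or frequencies, no adherence rates, no SDs and no planned number of episodes ("with the final number determined by site-level DKA admission volumes"). All distributions below are therefore assumptions, shown over a range. There is no figure in the plan to reproduce.

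**Counts (no distribution needed).** With n recommended checks, the passing counts are the whole numbers from 0.8n to 1.2n. A neighbouring count n ± 1 passes only if 0.2n ≥ 1, that is n ≥ 5.
- n = 4: limits 3.2 to 4.8, so only 4 passes. Three checks and five checks (5/4 = 125%) fail alike.
- n = 6: limits 4.8 to 7.2, so 5, 6 and 7 pass and 8 fails.
- n = 12: limits 9.6 to 14.4, so 10 to 14 pass.

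**Time to insulin, normal.** In-band share = Φ((1.2 − m)/s) − Φ((0.8 − m)/s), with mean m and SD s in units of T. The one-sided share with the same tolerance is Φ((1.2 − m)/s).

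| m | s | In band | At or under 1.2T |
|---|---|---|---|
| 1.40 | 0.42 | Φ(−0.48) − Φ(−1.43) = 0.32 − 0.08 = 0.24 | 0.32 |
| 0.92 | 0.42 | Φ(0.67) − Φ(−0.29) = 0.75 − 0.39 = 0.36 | 0.75 |
| 0.58 | 0.25 | Φ(2.48) − Φ(0.88) = 0.99 − 0.81 = 0.18 | 0.99 |

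The last in-band value is 0.19 with unrounded inputs (m = 35/60, s = 15/60), the figure used in the summary. From the late start (1.40 to 0.92) the score moves the right way, but gains 12 points against 43 one-sided. From the near-target start (0.92 to 0.58) it falls from 36% to 19%, while the one-sided share rises from 75% to 99%.

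**Time to insulin, log-normal.** Median falling from 1.0T to 0.6T:
- log-SD 0.3: in band 0.500 to 0.158; at or under 1.2T, 0.728 to 0.990.
- log-SD 0.5: in band 0.315 to 0.200; at or under 1.2T, 0.642 to 0.917.

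With a late start (median 1.5T to 1.0T) the in-band share rises: 0.210 to 0.500 and 0.223 to 0.315.

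**Monitoring frequency, normal ratio.** In-band share, with the share at or above 0.8 in brackets:

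| SD | Mean 0.70 | Mean 1.00 | Mean 1.30 |
|---|---|---|---|
| 0.15 | 0.252 (0.252) | 0.818 (0.909) | 0.252 (1.000) |
| 0.25 | 0.322 (0.345) | 0.576 (0.788) | 0.322 (0.977) |
| 0.35 | 0.311 (0.388) | 0.432 (0.716) | 0.311 (0.923) |

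From 1.00 to 1.30 the in-band share falls in all three scenarios. From 0.70 to 1.00 it rises. From 0.70 to 1.30 it does not change at all, because the two means lie equally far from 1.

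**The case against.** The strongest reply is that the scoring rule is partly inferred. The article does not say how a percentage is formed for insulin timing, the items are introduced as examples, and the common data dictionary mentioned under DEKODE implementation process may hold item-level coding that is not shown. This stands for the timing illustration, which rests on the literal ratio. It does not remove the point: the article itself fixes the band, names these items beside it and exempts none. The monitoring arithmetic follows more directly.

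The article also does not say which recommendations are limits, minima or target amounts, and an aim of reducing unwarranted variation is compatible with a two-sided band for some items. That stands. It cannot be assumed that monitoring well above the guideline is better care, and a two-sided rule may be intended for fluid.

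Three stronger readings are tempting and are not supported:
- A reader might infer that the sign of the effect will be reversed. It depends on the starting point. The Introduction describes adherence as inconsistent, so a start short of target is at least as plausible, and from there the score moves the right way. Departures within 20% are unaffected.
- A reader might infer that hospitals will be ranked or fed back on this band score. The quarterly reports are described only as summarising local process and outcome measures, and benchmarking appears under the secondary outcomes. Neither place says that the in-band score is used.
- A reader might infer that the remedy is to score at or before T, or at least the full recommended number. That would remove the protocol's 20% tolerance on the failing side: insulin at 1.1T or monitoring at 90% is adherent now and would become non-adherent.

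**Conclusion.** The point holds in a limited form. As written, a primary outcome applies one two-sided band to items of different kinds, and so cannot separate a departure of more than 20% in the favourable direction from one in the unfavourable direction. For items with fewer than five recommended checks, a single check either way fails.

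Under the assumed distributions, a shift from near target to better than target lowers the in-band share in every scenario, by 12 to 57 percentage points for monitoring (0.432 − 0.311 and 0.818 − 0.252) and by 12 to 34 for log-normal insulin times (0.315 − 0.200 and 0.500 − 0.158). A shift from well short of target up to target raises it, though by less than a one-sided score with the same tolerance. Understatement is thus the more general risk, and reversal is a possibility confined to sites already near target.

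These sizes rest on invented means and SDs, on the delivered ÷ recommended reading, and on insulin timing being a limit and monitoring a minimum. The count result needs only the ratio reading.

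**What to change.** Before analysis, add a scoring table that states for each adherence component how the percentage is formed and whether its limit is one-sided or two-sided. Keep the existing 20% tolerance:
- where the guideline sets a time limit, adherent means no more than 120% of it;
- where it sets a minimum frequency, adherent means at least 80% of it;
- where it sets a target amount, keep the two-sided 80–120% band.

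The investigators should classify each item from the guideline. If they intend a value above 120% (or a time below 80%) to count as non-adherent for a given item, the table should say so for that item. Report the components separately, and apply the same rule to the baseline, implementation and follow-up periods.

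The cost is one table and slightly more analysis. No new data are needed, because key timestamps, biochemical monitoring and treatment processes are already in the core dataset described under DEKODE implementation process.

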### Eligibility criteria and case definition

Eligible episodes will include adults aged ≥16 years who are admitted with DKA or who develop DKA during hospital admission at a participating centre during the study period. All types of diabetes will be eligible, provided that the episode meets the diagnostic criteria for DKA according to the Joint British Diabetes Societies (JBDS) DKA guideline.

In line with the JBDS DKA guideline, DKA will be defined by the presence of hyperglycaemia or known diabetes, ketonaemia or significant ketonuria, and metabolic acidosis. This will generally include capillary or blood ketones ≥3.0 mmol/L or significant ketonuria, venous or arterial pH <7.3 and/ or serum bicarbonate <15 mmol/L, alongside clinical assessment consistent with DKA.

Each DKA presentation will be treated as a separate episode for audit and feedback purposes. Recurrent DKA admissions in the same individual will therefore be included as separate episodes, as each presentation represents a distinct episode of care and an opportunity to evaluate DKA management.

Episodes will be excluded if the JBDS diagnostic criteria for DKA are not met, if the presentation represents isolated ketosis without acidosis, hyperosmolar hyperglycaemia state without DKA, or if essential data required to confirm DKA diagnosis are unavailable.

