### DEKODE implementation process

Interested participating hospitals will be provided with access to an online study folder containing the study protocol and data collection form, which will support local audit registration. Following local registration, each site will share its audit registration number with the central DEKODE team and attend a virtual onboarding meeting covering the study protocol, eligibility criteria, and data collection procedures.

Each participating site will identify a local centre lead, who will coordinate communication between the local team and the central DEKODE team. Data collection will primarily be undertaken by clinicians and medical students involved in the DEKODE project, following audit registration and training. Local audit, governance, and quality improvement structures will be engaged to support approval, oversight, and alignment of the initiative with existing hospital processes.

Implementation will involve site onboarding, local audit registration, training of local data collectors and clinical leads, standardised data collection through REDCap-based DEKODE platform, quarterly audit-and-feedback reports, and structured local action planning. Each hospital will obtain a patient list from its information team for adults aged ≥16 years who were admitted with DKA or developed DKA during admission. Patient-identifiable data will remain within the local hospital team and will not be shared with the central DEODE team. The central team will receive only pseudonymised data through REDCap.

Standardisation across participating sites will be supported through use of common study protocol, eligibility criteria, data collection form, data dictionary, and REDCap-based data submission platform. All sites will collect the same core dataset for each eligible DKA episode, including diagnostic criteria, key timestamps, biochemical monitoring, treatment processes, complications, and clinical outcomes. The virtual onboarding meeting and pilot review of five DKA episodes will be used to ensure that local data collectors interpret variables consistently before full data collection begins. This approach is intended to support comparable data collection, benchmarking, and cross-site learning while allowing local adaptation in how improvement actions are implemented.

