### Missing data

The extent and pattern of missing data will be summarised by variable, site, and study phase. For quantitative analyses, cases will be included where the required data for a specific outcome are available. Therefore, an episode with missing data for one secondary outcome may still contribute to analyses of other outcomes where the relevant data are complete. Episodes missing essential data required to confirm DKA diagnosis or calculate the primary outcome will be excluded from the relevant analysis. Where missingness is substantial or differs across sites or study phases, this will be reported and considered when interpreting the findings.

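### Overall length of stay is analysed for all episodes, including DKA that develops in hospital, so inpatient days before DKA began enter an outcome meant to show the effect of DEKODE

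*Protocol article*

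**What the plan says.** Under Quantitative data collection and outcomes, the protocol article names the key clinical outcomes, "namely in-hospital mortality, 30-day readmission rates for DKA, and overall length of hospital stay". Quality improvement and implementation measures repeats the item without a start point: "Clinical outcome measures will include time to DKA resolution, length of hospital stay". The other time outcome does have one: "DKA episode duration, defined as the time from diagnosis to biochemical resolution".

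Eligibility criteria and case definition admits two routes into the dataset: "adults aged ≥16 years who are admitted with DKA or who develop DKA during hospital admission at a participating centre". DEKODE implementation process uses the same two routes for the patient list each hospital draws up: "adults aged ≥16 years who were admitted with DKA or developed DKA during admission".

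Nothing narrows this for length of stay. Site selection and sample size rationale says that "all eligible adult DKA episodes identified during the baseline, implementation, and follow-up periods will be included". The only outcome-specific rule, under Missing data, concerns data availability: "cases will be included where the required data for a specific outcome are available".

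The outcomes are to be analysed by interrupted time series to assess change attributable to DEKODE. Early adopters are to be compared with new implementers, and each site with the pooled data.

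**The concern.** For a patient admitted with DKA, overall stay and stay from DKA onwards are nearly the same. For a patient who develops DKA during an admission for something else, overall stay also contains every day before DKA began. Feedback on DKA care cannot shorten those days.

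Three things are at stake:

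- **Precision.** A minority of episodes carries a long extra component, which inflates the variance of stay.
- **Relative effect.** The same absolute reduction is a smaller percentage of a larger mean.
- **Comparability.** A hospital with more in-hospital onset shows a longer mean stay whatever the quality of its DKA care. The same happens between phases if the onset mix shifts.

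**Working it through.** The article gives no effect size, standard deviation, power or target number of episodes for length of stay, so it has no figure to reproduce. The check is whether the text leads to the problem, and how large it could be.

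**Reading the text.** In-hospital onset is eligible, all eligible episodes are included, and the outcome is overall stay. The same paragraph starts episode duration at diagnosis and does not do so for stay. Admission to discharge is therefore the natural reading.

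**Model.** Let *q* be the share of episodes with in-hospital onset. Let *m* be the mean number of days before DKA in those episodes, exponentially distributed and independent of the later stay. Then:

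- increase in mean stay = *q·m*
- increase in variance = *q·2m² − (q·m)²* = *q·m²·(2 − q)*

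**Size.** Assumed, not from the article: stay from DKA onwards is exponential with mean 5 days (variance 25), *q* is 3–15%, *m* is 5–10 days. The last column shows a true 1-day reduction as a percentage of mean overall stay; it would be 1/5 = 20% without prior days.

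| *q* | *m* | Added mean (days) | Added variance | Variance ratio | 1 day as % of mean |
|---|---|---|---|---|---|
| 3% | 5 | 0.15 | 0.03×25×1.97 = 1.48 | 1.06 | 1/5.15 = 19.4% |
| 3% | 10 | 0.30 | 0.03×100×1.97 = 5.91 | 1.24 | 1/5.30 = 18.9% |
| 15% | 5 | 0.75 | 0.15×25×1.85 = 6.94 | 1.28 | 1/5.75 = 17.4% |
| 10% | 10 | 1.00 | 0.10×100×1.90 = 19.0 | 1.76 | 1/6.00 = 16.7% |
| 15% | 10 | 1.50 | 0.15×100×1.85 = 27.75 | 2.11 | 1/6.50 = 15.4% |

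A simulation of 400,000 episodes on the same assumptions gave matching values at 3%/5, 10%/10 and 15%/10 days.

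**Power, on a second set of assumptions.** Stay from DKA onwards has mean 4 and SD 4 days, the true reduction is 1 day, two-sided alpha is 0.05, and the comparison is a simple before/after one rather than the planned time series. Then *n* per period = 2·(1.960 + 0.842)²·SD²/1² ≈ 15.7·SD². With SD² = 16 this gives 252 per period for 80% power. With overall stay, SD² = 16 + *q·m²·(2 − q)*:

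| *q* | *m* | SD | Power at 252 per period | Episodes per period for 80% |
|---|---|---|---|---|
| 2% | 5 | 4.12 | 78% | 267 |
| 5% | 10 | 5.07 | 60% | 405 |
| 10% | 10 | 5.92 | 48% | 550 |
| 15% | 15 | 8.86 | 24% | 1232 |

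The last row lies outside the 5–10 day range above and is an extreme.

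**Bias.** Expected overall stay at time *t* is *μ(t) + q(t)·m(t)*, where *μ* is mean stay from DKA onwards. If *q* and *m* are constant, the extra term is constant and the absolute level and slope changes are those of *μ*, so there is no bias. If *q* moves from 5% to 10% with *m* = 10, mean stay rises by 0.05 × 10 = 0.5 day with no change in care (0.25 day for *m* = 5, 0.75 day for *m* = 15). Between two hospitals, the difference in level is off by (*q*₁ − *q*₂)·*m* even if both shares are stable over time. In an assumed quarter of 15 episodes at one site, a single in-hospital-onset episode with 10 prior days moves the mean by 10/15 ≈ 0.7 day.

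**The case against.** **The start point is not stated.** The article never says that stay runs from admission for in-hospital onset. A data dictionary and a full protocol or analysis plan may settle it. This stands as a caveat, and a missing definition alone would be no finding in a condensed article. But the article does choose overall stay, with in-hospital onset eligible, beside an outcome it anchors at diagnosis. The problem comes from that combination.

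**The more direct measures are unaffected.** Episode duration starts at diagnosis, and adherence and iatrogenic complications do not depend on when stay begins. Length of stay is introduced after the outcomes called primary. This stands and limits the weight of the point.

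**Bias needs a changing or differing onset mix.** This also stands. The article gives no sign that the mix will change between phases. It does plan comparisons between hospitals, for which nothing suggests that the mix is equal.

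**The size is assumed.** True, and at the low end it is minor. The variance figures are on the raw scale; a median or log-scale analysis would be less sensitive.

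**Timing from diagnosis is only a partial cure.** True: days after diagnosis can still be driven by the illness that brought the patient in. Onset types therefore need to be separated as well.

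**Two stronger readings are not supported.** A reader might infer that DEKODE will detect more in-hospital DKA and so lengthen reported stay. But cases come from hospital information-team lists, no change of case finding by phase is described, and the feedback concerns management of DKA. A reader might also infer that one stay is counted twice when two episodes fall in one admission. The episode rule is explained through recurrent admissions, and two episodes within one admission are not described.

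**Conclusion.** The point holds in a limited form. Under the stated eligibility and outcome, and on the plain reading of overall stay, inpatient days before DKA enter length of stay. The certain consequences, if any such episodes occur, are added variance and a diluted relative effect. The absolute time-series change is not biased while the onset mix and prior days are stable. Comparisons between phases or sites are biased to the extent that these differ, and the planned site benchmarking is the most exposed.

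The size cannot be known from the article. On the assumed 3–15% in-hospital onset and 5–10 prior days, mean stay rises by 0.15–1.5 days and raw-scale variance by about 6–110%. The power figures are illustrations from a simple before/after comparison and do not describe the planned analysis. The outcomes named as primary are untouched, so this is a correction worth making and does not threaten the study as a whole.

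**What to change.** - Define length of stay for analysis as time from DKA diagnosis to discharge, for every episode.
- Record onset type, and report and analyse admitted-with-DKA and in-hospital-onset episodes separately. Alternatively, make admitted-with-DKA episodes the main length-of-stay analysis. Use the same split in the site benchmarking.
- Report the share of in-hospital onset by site and phase, so that a reader can see whether the mix differs.
- Keep overall stay, if wanted, as a descriptive measure.

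The cost is small. Diagnosis time is already needed for episode duration, and admission and discharge times for length of stay, so onset type should be derivable with little or no new data collection. The data dictionary should be checked to confirm this. The downside is less direct comparability with earlier DEKODE reports of overall stay, which the descriptive measure would largely preserve.
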